### Missing data

Data will be routinely monitored by the investigators to ensure completeness; it will be visually inspected for errors, omissions, and data outside the limit ranges. A Consolidated Standards of Reporting Trials (CONSORT) diagram will be produced at the end of the study (Schulz et al., 2010). We expect that study loss to follow-up will be moderate (30%) due to our multi-pronged retention approach. If participants are reincarcerated, they will continue to be eligible to participate once they return to the community if they are within the 12-month study participation period. Per our retention plan, substantial efforts will be made to ensure complete follow-up. Rates of missing data and loss to follow-up will be reported. For the primary aim, the mixed-effects regression will yield consistent regression parameter estimates provided that the missing data are missing at random, a reasonable assumption when there are sufficient covariates considered in the analysis (Liu, 2015). Alternative missing data strategies, such as missing data imputation strategies or propensity weighting, will be considered based on the degree of missingness in the data but will not be applied without extensive sensitivity analysis. Under these various missing data strategies, the statistical analysis will be run and compared for consistency. When serious deviations are observed, the impact of the missing data will be evaluated to see if that is the source of the discrepancy.

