### Follow-up surveys & incentives to support retention

We will provide escalating incentive gift cards for survey-based data collection visits conducted at 6-months ($30) and 12-months ($50); these data will enable the researchers to assess participants’ use of health-supporting institutions over time. At baseline, we will collect participant locator forms for up to 5 persons who can help contact the participant, if needed and send visit reminders via text/email/phone call, per participant preference. We will provide $5 participant gift cards for monthly check-ins over months 7–12 in order to promote participant retention.

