### Analysis of key secondary outcome (safety)

All participants will be included in a safety analysis. Adverse Events (AEs) and Serious AEs (SAEs) will be listed by participant. AEs will be summarized by method of collection type, frequency, severity, relationship to study intervention, any change in study intervention, and number of participants per treatment. The frequency of AEs and SAEs will be described by group and compared using Fisher’s exact test.

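### The all-participant Fisher comparison of adverse events makes no allowance for people partly or wholly unobserved through loss or custody

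*Protocol article*

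**What the plan says.** The section on the key secondary outcome (safety) fixes the population: "All participants will be included in a safety analysis". It fixes the presentation as well: "Adverse Events (AEs) and Serious AEs (SAEs) will be listed by participant", and "The frequency of AEs and SAEs will be described by group" and compared with Fisher's exact test. It mentions no observed time and does not say how an incompletely followed person is handled.

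The Missing data section expects moderate loss to follow-up of 30%. For participants who are reincarcerated it says that "they will continue to be eligible to participate once they return to the community if they are within the 12-month study participation period". Its missing-at-random argument is made for the primary aim. Imputation and weighting are offered as alternatives, but nothing ties them to the safety comparison. The section also promises that "Rates of missing data and loss to follow-up will be reported" and that "A Consolidated Standards of Reporting Trials (CONSORT) diagram will be produced at the end of the study".

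For tracing, the section on follow-up surveys and incentives says "we will collect participant locator forms for up to 5 persons who can help contact the participant", and it provides paid monthly check-ins in months 7 to 12.

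**The concern.** Fisher's exact test on participants needs each person to be a case or a non-case, and it has no cell for unknown status. With everyone in the denominator and a sizeable share expected to be lost, a person who was not observed adds one to the denominator and, unless an event was learned of some other way, nothing to the numerator.

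Two things are at stake. The absolute AE and SAE rates, which readers will take as the safety profile of the programme, would be too low in both arms. The between-arm comparison would also mix event risk with completeness of observation, so that the arm that keeps more people in view would look the more harmful. Custody is a foreseeable reason for a gap in this population, and the document treats it only as a question of re-entry.

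**Working it through.** **Inputs from the article.** 300 enrolled, 1:1, so 150 per arm; 30% attrition; 208 analysable participants, 104 per group (Power & sample size; Study arms & randomization).

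**The plan's own figure.** 300 × (1 − 0.30) = 210, against 208 stated. In reverse, 208 / 0.70 = 297.1, so 298, against 300 stated. The attrition figure reproduces within rounding, and the expected number lost is 300 × 0.30 = 90.

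**Assumptions, not in the article.** The true AE risk is the same in both arms and the same in people observed and unobserved. No event is captured in anyone unobserved. Loss by arm is varied.

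**Formula.** Apparent rate in an arm = true risk × (1 − fraction unobserved). When true risk is equal, the apparent risk ratio = (1 − fraction unobserved, treatment) / (1 − fraction unobserved, control), and the risk cancels.

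**Effect on absolute rates.** With 30% unobserved in both arms, the apparent rate is 0.70 times the true rate: 10% reads as 7.0%, and 12% as 8.4%. The relative shortfall is 30%. It is smaller to the extent that lost people were observed for a while before leaving. It could be larger if lost or detained people carry a higher risk than those retained.

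**Effect on the arm comparison.**

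| Unobserved, treatment / control | Apparent rates at 10% true risk | Apparent risk ratio | Fisher p at 10% true risk |
|---|---|---|---|
| 30% / 30% | 7.0% / 7.0% | 1.00 | 1.00 |
| 20% / 40% | 8.0% / 6.0% | 1.33 | 0.65 |
| 40% / 20% | 6.0% / 8.0% | 0.75 | 0.65 |
| 10% / 50% | 9.0% / 5.0% | 1.80 | 0.27 |

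Each split averages to the planned 30%. For the second row the expected counts are 150 × 0.10 × 0.80 = 12 and 150 × 0.10 × 0.60 = 9, and 12 / 9 = 1.33. The p-values use expected counts rounded to whole people. A spurious significant result needs both a wide split and a common event: the 10%/50% split gives p = 0.015 at a true risk of 30%.

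**The same data with observed people as denominator.** Second row: 12 / (150 × 0.80) = 12 / 120 = 10%, and 9 / (150 × 0.60) = 9 / 90 = 10%. The risk ratio is 1.00 and the true rate is recovered. Under these assumptions the same holds for the other rows, and an observed-time denominator extends it to people followed for part of the period.

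**The case against.** The strongest reply is that this is a condensed article. AE definitions, the collection schedule, sources of information and vital-status tracing usually sit in the full protocol, which is not shown. That stands: their absence here is no finding, and nothing above relies on it. The article's intention to summarise AEs by how they were collected also suggests that collection methods exist that it does not describe.

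A reader might infer more than the text supports:

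- **That unobserved people are counted as event-free by rule.** No section says so. It is the practical result of a per-participant test over everyone when nothing else is specified.
- **That AE recording stops in custody.** The sentence on reincarceration is a re-entry rule. It lets people resume rather than be withdrawn, and it is silent on safety recording. Someone released before a survey may report events from the gap.
- **That death or reincarceration by arm can never be established.** SAEs are listed by participant, loss rates and a CONSORT diagram are promised, and locator contacts and check-ins allow some tracing. Nothing prevents known deaths or custody from being reported by arm.
- **That reincarceration is the only adverse course considered.** Days in hospital and delayed care are among the listed outcomes.

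It is also fair to say that equal loss leaves the risk ratio at 1.00, that no difference between arms is documented, and that the primary analysis is untouched. All of this limits the point. It does not remove it, because the population and the test are choices that the article does fix. Loss rates and a flow diagram describe the missingness but do not put observed time into the safety comparison.

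**Conclusion.** The point holds as a cheap improvement to the stated safety analysis. It is not a design fault or a contradiction between sections. Followed as written, the comparison uses a denominator that the plan itself expects to contain about 90 incompletely observed people.

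Absolute rates would be understated by at most 30% in relative terms if lost people share the risk of the others. Bias between arms arises only with unequal loss or custody: a risk ratio of 1.33 or 0.75 for an assumed 20%/40% split. At a 10% true risk that would be far from significant, so the main harm is misleading reported rates rather than a false signal.

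The article gives no custody rate and no loss by arm. Unequal loss is plausible, because treated participants have 12 coaching and up to 12 navigation sessions while controls have two Navigator sessions, but that is a reason to look and not evidence of a difference. The 30% is itself uncertain: the article describes 66 of 148 pilot participants as retained to 6 months, in a different population and design.

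**What to change.** In the safety section, keep the all-participant Fisher comparison and add beside it, by arm:

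1. person-months observed, with a rule set before arms are compared for what counts as an observed month;
2. participants with at least one AE, and with at least one SAE, per observed person-month, counting time to the first such event or to the end of observation;
3. known end-of-study status: completed, in custody, dead, or lost.

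All of this can be built from the survey, check-in and locator information that the trial already collects. It needs no new visits, no tracing campaign and no safety contacts after month 12.

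The cost is a little extra tabulation, and rates that may look less favourable than the all-participant ones. Two limits should be stated with the table. Observed-time rates assume that risk is similar in observed and unobserved time. They also do not correct for the treatment arm being seen more often by the staff who record adverse events, which is a separate question of ascertainment.

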### Qualitative interviews: sampling, data collection & analysis

This mixed-method RCT also involves individual, semi-structured qualitative interviews, which are expected to last ~ 30 min and will occur with a sub-sample of participants at 6 and 12-months (with escalating incentives of $30 and $50). Interviews will explore immediate satisfaction with the curriculum, impacts of the intervention and maintenance of the knowledge and skills learned. We expect that many participants will experience challenges to engaging with the healthcare system, though this may not apply to all participants. Thus, we will employ purposive sampling to identify participants (*n* = 40, stratified by arm) who reported ≥ 1 healthcare access barriers at baseline (e.g., no recent doctor visit, uninsured status, and/or no regular source of care) (Johnson, 1990; Patton & Patton, 2002). This approach will allow us to more deeply explore the impact of the intervention on the treatment group as well as how the control group engaged with the study materials and their perceived impact on the outcome of interest. We will also attempt to recruit participants who did not complete the 6-month follow-up survey to ensure that their perspectives are included. The minimum number of interviews conducted for qualitative studies is expected to range from 15–20 (Malterud et al., 2016). By this standard, we anticipate that our sample size of 20 participants per intervention arm (*n* = 40 total) will be adequate for achieving thematic saturation within key topics of interest.

We use a deductive thematic approach to analyze the qualitative interview data as described below. Interviews will be digitally recorded, transcribed, and analyzed using team-based consensus methods (Willms et al., 1990). Specifically, analysts will first develop primarily deductive codes by reviewing key questions from interview guides and 2–3 interview transcripts. They will independently test preliminary codes by applying them to a second set of 2–3 transcripts and then meet to assess consistency in code application (i.e., reliability), resolve discrepancies, enhance code definitions, and finalize the codebook. A template approach (Crabtree & Miller, 1992) will be used to support thematic analysis and publication development; we will compare participants’ responses to the topics of interest as well as emergent topics related to health care utilization and intervention impacts.

### Limitations

Potential challenges to study implementation include identification of eligible JIA and participant attrition. However, the study employs a venue-based recruitment strategy wherein organizations that serve justice impacted persons are targeted for outreach and recruitment. We employ escalating incentives, locator forms, and monthly check-ins during the follow-up period to ensure that we have the latest contact information. These strategies are designed to foster participant retention.

## Discussion

Studies to build health literacy among justice-impacted adults are sorely needed given the challenges this vulnerable community faces in coordinating across multiple systems to meet basic needs and improve or maintain health and wellbeing. This study will leverage the strengths of quantitative and qualitative longitudinal methods to provide a breadth and depth of understanding regarding the effectiveness of the health literacy intervention described in this study. If successful, results may shift the paradigm of service delivery for JIA from a focus on single issues to comprehensive strategies that address JIA’s knowledge, skills, and self-efficacy to support sustained healthcare access. Importantly, the knowledge and skills learned are also applicable across other life domains and effective strategies are urgently needed amidst an evolving social, economic, and healthcare landscape. The long-term goal of this work is to improve healthcare access and reduce health disparities among JIA. If proven effective, the UCSD RELINK health literacy intervention may inform theory for interventions designed to reduce health disparities among JIA, the content and approach of service delivery models for JIA, and policies to fortify JIA’s health in institutional and community settings. Findings will also significantly expand our understanding of best practices for engaging and retaining JIA in health and longitudinal studies. Results may also inform our understanding of the scalability of this intervention in clinical and non-clinical settings.

## Data Availability

Not applicable; no data are presented in this article describing the study protocol.

## Abbreviations

JIA: Justice-impacted adults
RCT: Randomized Clinical Trial
UCSD RELINK Program: University of California San Diego Re-Entry Community Linkages Program
